### Quality control, data management, and monitoring

3.9

A detailed investigator’s manual has been developed prior to the start of the clinical trial, and all participating members of the study will be trained. Standard operation procedure (SOP) is strictly followed at every step of the process. Each participant has a unique case report form (CRF) for recording raw data, and all original CRFs are sealed by the project leader at the end of the trial. The designated investigator enters the raw data via a pre-designed, password-protected data management platform, and the data manager is blinded to verify the consistency of the original CRFs and the spreadsheets. An ombudsman (usually a panel of experts or an ethics committee) will intermittently monitor the acupuncturist and each step of the trial to protect the rights of the participants and ensure the quality of the study.

### Statistical analysis

3.10

All statistical analysis will follow the intention-to-treat (ITT) principle, and the missing values will be supplemented by last observation carried forward (LOCF). For variables with normal distribution, one-way analysis of variance (ANOVA) will be used for comparison inter-group comparison, and paired samples *t*-test will be used for intra-group comparison. Kruskal-Wallis test will be used for non-normal distributed variables. Repeated measurements at different time points will be analyzed by using repeated-measures ANOVA. Data values will be mainly presented as the mean ± standard deviation or the median ± quartile spacing. While Chi-Square test/Fisher’s Exact test will be adopted to analyze categorical data. Categorical variables will be expressed as numbers and percentages. All statistical tests being bilateral at *p* < 0.05. Data analysis will be performed using IBM SPSS version 26.0 software (IBM Corp, New York).

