### Sample size

3.5

Sample size estimation was based on the change in the primary outcome ISI score. Based on the results of existing studies in the literature, the ISI score after 4 weeks of treatment was (10.5 ± 3.8) points (32), and we expected that after 6 and 8 weeks of treatment, the ISI score would decrease by 1 point and 2.5 points. With the test level set at *α* = 0.05 and the test efficacy at 1-β = 0.9, plus calculations based on the mean comparison formula of multiple independent samples yielded 58 cases in each group. Considering a 15% dropout rate, the three groups are evenly divided at 1:1:1, with 67 cases required in each group, for a total of 201 participants are needed for this trial.

Sample size estimation formula:

$$n=\frac{\psi^{2}\left(\sum_{j=1}^{k}s_{j}^{2}/k\right)}{\sum_{j=1}^{k}{\left({\bar{X}}_{j}-\bar{\bar{X}}\right)}^{2}/\left(k-1\right)}$$

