### Intervention

3.6

Participants in the three groups receive the same acupuncture treatments three sessions a week with at least 1 day between the two treatments: Group A (12 sessions for 4 weeks), Group B (18 sessions for 6 weeks), and Group C (24 sessions for 8 weeks). The acupoints will be selected as Baihui (GV20), Yintang (GV29), Anmian (EX-HN22, bilaterally), Shenmen (HT7, bilaterally), Neiguan (PC6, bilaterally), and Sanyinjiao (SP6, bilaterally). The localization of the acupoints refers to the national standards of the People’s Republic of China issued by the State Bureau of Technical Supervision, “Nomenclature and location of acupuncture points” (GB/T12346-2006) and “Nomenclature and location of extra points in common use” (GB/T 40997–2021). The localization of the acupuncture points is shown in Figure 2.

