##### PSQI

3.7.3.1

PSQI is used to rate the quality of a participant’s sleep in the previous month and consists of 18 items, comprising 7 components. This includes subjective sleep quality, sleep latency, sleep duration, habitual sleep efficiency, sleep disturbance, used sleep medication, and daytime dysfunction. Each component is scored from 0 to 3, and the cumulative score of each component is the PSQI total score. The total score ranges from 0 to 21, with higher scores indicating poorer sleep quality. Our prespecified primary endpoint is at the end of treatment and the secondary endpoint is 3 months after the end of treatment.

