##### FSS

3.7.3.4

FSS has a total of 9 items, each scored on a scale of 1–7, with higher scores being associated with greater fatigue.

Primary and secondary outcomes will be evaluated at the following time points: Group 1 (0, 4 weeks), Group 2 (0, 4, 6 weeks), Group 3 (0, 4, 6, 8 weeks), and at follow-up (the first and third month after the end of treatment). The study schedule is depicted in Table 2.

**Table 2 tab2:** Study schedule.

Study period	Observation	Baseline	Treatment phase	Follow-up	
Timepoint	<7 days	0 week	4, 6, or 8 weeks	1 month	3 months
Enrollment					
Eligibility	×				
Informed consent		×			
Allocation		×			
Interventions					
Group 1			×		
Group 2			×		
Group 3			×		
Outcomes					
ISI		×	×	×	×
PSQI		×	×	×	×
SDS		×	×	×	×
SAS		×	×	×	×
FSS		×	×	×	×
Use of sleep medications			×	×	×
ISI < 8 points			×	×	×
Adverse events			×		

PSQI, Pittsburgh Sleep Quality Index; ISI, Insomnia Severity Index; SDS, Self-Rating Depression Scale; SAS, Self-Rating Anxiety Scale; FSS, Fatigue Severity Scale.

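### LOCF is the only missing-data rule, but the visit schedule makes it act differently in each arm: at end of treatment, Group A dropouts can carry only baseline

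*Protocol article*

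**What the plan says.** The Statistical analysis section (3.10) applies the intention-to-treat principle and says that "the missing values will be supplemented by last observation carried forward (LOCF"). No other missing-data method appears. Between-group comparison of normally distributed outcomes is by one-way ANOVA.

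The treatment lengths are "Group A (12 sessions for 4 weeks), Group B (18 sessions for 6 weeks), and Group C (24 sessions for 8 weeks"). The assessment times, given at the end of the FSS section (3.7.3.4), are "Group 1 (0, 4 weeks), Group 2 (0, 4, 6 weeks), Group 3 (0, 4, 6, 8 weeks), and at follow-up" one and three months after treatment ends. That section numbers the groups 1 to 3 rather than A to C, but the weeks match.

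The primary time point is printed under PSQI (3.7.3.1): "Our prespecified primary endpoint is at the end of treatment and the secondary endpoint is 3 months after the end of treatment". The Sample size section (3.5) also compares ISI at the end of each course. It takes from the literature that "the ISI score after 4 weeks of treatment was (10.5 ± 3.8) points", expects that "after 6 and 8 weeks of treatment, the ISI score would decrease by 1 point and 2.5 points", and adds participants for loss: "Considering a 15% dropout rate". It does not say when that loss occurs.

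**The concern.** The trial asks whether end-of-course ISI differs by course length. Course length also determines how many earlier scores LOCF can draw on: Group A has no post-baseline score before its end-of-treatment visit, Group B has one (week 4) and Group C has two (weeks 4 and 6). The imputation rule therefore varies with the randomised factor.

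Two kinds of harm are possible. If A dropouts are filled with untreated scores more often than C dropouts, A looks worse and a course-length effect can appear where none exists. If ISI keeps falling with treatment, as the planning values assume, carrying early scores forward shrinks a real difference and widens the spread of scores.

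For the three-month endpoint, LOCF carries the last available score forward for anyone lost in follow-up, so it cannot show relapse in those participants.

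**Working it through.** **Inputs from the protocol.** Planned ISI means: 10.5, then 10.5 − 1 = 9.5, then 10.5 − 2.5 = 8.0. SD 3.8, α 0.05, power 0.90, 58 per arm before loss, 67 after, 15% dropout.

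**Assumptions.** Mean baseline ISI B = 14, 17 or 20 (the protocol gives only the entry minimum of 10). For the simulations: correlation 0.5 with baseline and 0.7 between later visits, and dropout unrelated to outcome.

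**The plan's own figure.** The grand mean is 9.33, and the squared deviations sum to 1.361 + 0.028 + 1.778 = 3.167, which is 1.583 after division by k − 1 = 2. With ψ = 2.52, n = 2.52² × 14.44 / 1.583 = 57.9, so 58 is reproduced. 58 × 1.15 = 66.7 gives 67. With 15% lost, 67 × 0.85 ≈ 57 have an observed score, which keeps power near 0.89.

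**What LOCF enters at end of treatment**

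| Time of loss | A | B | C |
|---|---|---|---|
| Before week 4 | baseline | baseline | baseline |
| Weeks 4–6 | – | week 4 | week 4 |
| Weeks 6–8 | – | – | week 6 |

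**Pattern (a): 15% lost in each arm, evenly over its own course; all arms truly end at 10.5.** The share of dropouts carrying baseline is 4/4 in A, 4/6 in B and 4/8 in C.
- Bias in A = 0.15 × (B − 10.5).
- Bias in C = 0.075 × (B − 10.5).
- False A–C gap = 0.075 × (3.5, 6.5, 9.5) = 0.26/0.49/0.71.

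**Pattern (b): constant weekly loss reaching 15% at week 8; planned means.**
- Still present at week 4: 0.85^0.5 = 0.922. At week 6: 0.85^0.75 = 0.885. At week 8: 0.85.
- A = 0.922 × 10.5 + 0.078 × B.
- C = 0.85 × 8.0 + 0.078 × B + 0.0367 × 10.5 + 0.0353 × 9.5.
- A–C = 9.68 − 7.52 = 2.16 instead of 2.5, whatever B is.
- Of the 0.34 lost, 0.078 × 2.5 = 0.20 comes from losses before week 4, which carry baseline in all arms alike. The other 0.0367 × 2.5 + 0.0353 × 1.5 = 0.14 comes from C's carried week-4 and week-6 scores.
- With no true difference the false gap is zero, because the share carrying baseline is 0.078 in every arm.
- Power still depends on B because mixing in baseline scores adds variance. In A at B = 20 this is 0.078 × 0.922 × 9.5² ≈ 6.5, on top of 14.44.

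**Pattern (c): 15% lost by month 3, constant rate within each arm.** Taking three months as 13 weeks, the share lost before week 4 is 1 − 0.85^(4/17) = 0.0375 in A and 1 − 0.85^(4/21) = 0.0305 in C. The false gap is 0.0070 × (3.5, 6.5, 9.5) = 0.02/0.05/0.07, and the planned gap stays about 2.4.

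**Simulated one-way ANOVA after LOCF, 67 per arm, B = 14/17/20**

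| Pattern | Type I error | Power under planned means |
|---|---|---|
| (a) | about 0.07/0.08/0.11 | about 0.88/0.87/0.84 |
| (b) | nominal | about 0.79/0.72/0.64 |
| (c) | nominal | about 0.90/0.86/0.85 |

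Analysing only observed end-of-treatment scores in the same settings keeps error nominal and power about 0.89–0.92.

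**The case against.** The strongest reply is that the size rests on dropout timing that the protocol does not state. That is correct.

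- Pattern (a) needs A to lose participants about twice as fast per week as C (15% over 4 weeks against 15% over 8). Nothing in the document supports that, and the false-positive risk depends on it.
- Pattern (b) gives no spurious effect, and more than half of its shrinkage comes from losses that are treated alike in all arms.
- Under pattern (c), which fits a trial followed to month 3, the effect on the primary time point is small.

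It can also be said that a participant who stopped in week 5 need not have reached the full-course mean, so carrying a week-4 score is not necessarily too high under intention-to-treat. The document does not settle this. The shrinkage in (b) assumes that dropouts would have reached it.

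Some stronger readings are tempting but unsupported. A reader might infer that LOCF both inflates false positives and removes a large share of power, but these harms arise under different dropout patterns. A reader might infer that LOCF always favours the longer courses, but the direction is not fixed. A reader might measure the power loss from 0.94, but that is the power with 67 complete per arm; the fair comparators are the planned 0.90 and about 0.89 with 57 observed.

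What stands is the mechanism. It follows from the stated rule and the stated schedule, and nothing in the protocol offsets it.

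**Conclusion.** The point holds in a limited form. At end of treatment every A dropout carries baseline. B and C dropouts carry baseline only if lost before week 4, and an on-treatment score otherwise. A participants lost in follow-up do have a week-4 score to carry.

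The direction and size of the bias cannot be fixed from the protocol. Across the three patterns the result runs from a minor power loss with nominal error, through type I error of up to about 0.11, to power of about 0.64 against the planned 0.90. These figures rest on assumed baseline means, assumed correlations and dropout unrelated to outcome. A reader of the results could not easily tell whether LOCF had created part of a course-length effect or hidden part of one. In the same settings, using the observed scores avoids both problems. The rule is worth changing before analysis, but the point does not invalidate the design.

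**What to change.** In the Statistical analysis section, replace LOCF as the primary rule with one of two methods: a likelihood-based mixed model on all observed ISI visits, or multiple imputation within arm using baseline and interim ISI. Keep LOCF only as a sensitivity analysis.

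Both methods use visits that are already scheduled, so sample size and design do not change. The cost is a little more analysis work and reliance on a missing-at-random assumption, which should be stated. Collecting ISI from participants after they stop treatment would be a separate, small operational step and is not needed for this fix.

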#### General information

3.7.1

(1) Participant demographics: gender, age, disease duration, educational level, occupation, sleeping environment, living environment, daily living situation, personality preference, income satisfaction, marital satisfaction, exercise habits.(2) Vital signs: body temperature, heart rate, breathing, pulse, blood pressure, body mass index.

Baseline data are required to be completed within 48 h of randomization. Heart rate, pulse, and blood pressure will be assessed before and after each acupuncture treatment.

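### The named between-group test for ISI has no baseline term although baseline ISI is collected in every arm; ANCOVA would gain power at almost no cost, and the wording on change and on baseline timing needs tidying to match.

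*Protocol article*

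**What the plan says.** **Analysis (3.10).** For normally distributed variables, "one-way analysis of variance (ANOVA) will be used for comparison inter-group comparison". Kruskal-Wallis is the fallback for non-normal variables, paired t-tests serve within-group comparisons, and repeated-measures ANOVA is listed for repeated measurements. No covariate is named, and no model is singled out as primary.

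**Sample size (3.5).** "Sample size estimation was based on the change in the primary outcome ISI score". The inputs that follow, however, are a post-treatment mean and SD for the 4-week course (10.5 and 3.8), with the expectation that "after 6 and 8 weeks of treatment, the ISI score would decrease by 1 point and 2.5 points". The result is 58 per arm, raised to 67 for dropout.

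**Data collected (3.3, 3.7.3.4, Table 2).** ISI is scheduled at week 0 in every arm. An ISI of at least 10 is also an entry criterion, so a score exists before enrolment.

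**Timing of baseline (3.7.1).** "Baseline data are required to be completed within 48 h of randomization". The sentence does not say before or after. Section 3.4 says that participants cannot be blinded, and Table 2 puts baseline ISI and allocation in the same column.

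**The concern.** A baseline value of the primary outcome is available for everyone, yet the between-group test that the plan names ignores it. If baseline and end-of-treatment ISI are correlated, part of the residual variance could be removed for one degree of freedom and no extra data.

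Two nearby wordings complicate this. Section 3.5 speaks of change but computes from a final score, so a reader cannot tell whether the ANOVA is to be run on the score or on the change. The two have different variances and different power. Section 3.7.1 leaves the order of baseline assessment and allocation open. That matters more once baseline enters the primary model, because a self-rating made after learning of a 4-week or 8-week allocation could be coloured by expectation.

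**Working it through.** **Inputs from the documents.** Arms k = 3; expected end-of-treatment means 10.5, 9.5 and 8.0 (falls of 1 and 2.5, both from the 4-week value); common SD 3.8; alpha 0.05 and power 0.9 (3.5); 58 evaluable per arm.

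**Inputs assumed.** The baseline-endpoint correlation r is not given; I use 0.3 to 0.6, with 0 as the worst case. For change scores only, I also assume a baseline SD of 3.8, because the documents give none.

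**Step 1: reproduce 58.** The grand mean is 28/3 = 9.333. The squared deviations are 1.3611 + 0.0278 + 1.7778 = 3.1667, and dividing by k − 1 = 2 gives 1.5833. With ψ = 2.52 and 3.8² = 14.44, the protocol's formula gives n = 2.52² × 14.44 / 1.5833 = 57.9, so 58. Reading the two falls as sequential (means 10.5, 9.5, 7.0) gives 6.3504 × 14.44 / 3.25 = 28.2, so that reading was not used. The 58 is therefore reproduced as an unadjusted one-way comparison of final ISI scores.

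**Step 2: power of the plan as sized.** Noncentrality λ = 58 × 3.1667 / 14.44 = 12.72 on 2 and 171 df. Noncentral-F power is 0.896, in line with the 0.90 target; exactly 0.90 needs 59 per arm.

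**Step 3: ANCOVA on baseline ISI.** Residual SD = 3.8 × √(1 − r²), so λ becomes 12.72 / (1 − r²) on 2 and 170 df.

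**Step 4: ANOVA on change from baseline.** With equal SDs, the SD of change = 3.8 × √(2(1 − r)), so λ becomes 12.72 / (2(1 − r)).

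| r | ANCOVA residual SD | ANCOVA power, 58 per arm | ANCOVA n per arm for 90% | Change SD | Change-score power, 58 per arm |
|---|---|---|---|---|---|
| 0 | 3.80 | 0.896 | 59 | 5.37 | 0.603 |
| 0.3 | 3.63 | 0.923 | 54 | 4.50 | 0.767 |
| 0.4 | 3.48 | 0.942 | 50 | 4.16 | 0.832 |
| 0.5 | 3.29 | 0.964 | 45 | 3.80 | 0.896 |
| 0.6 | 3.04 | 0.983 | 38 | 3.40 | 0.952 |

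The residual variance falls by r², that is by 9% at r = 0.3 and by 36% at r = 0.6. At r = 0 the lost degree of freedom costs less than 0.1 percentage point of power. With equal SDs, ANCOVA has the smaller variance for any r below 1, because 1 − r² = (1 − r)(1 + r) is less than 2(1 − r). Change scores match the unadjusted final score at r = 0.5, do worse below it and better above it.

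**Step 5: does repeated-measures ANOVA already cover this?** With two times, baseline and end of treatment, its group-by-time test is the change-score ANOVA of step 4. With more times the arms do not share a grid: 3.7.3.4 schedules treatment-phase visits at weeks 0 and 4; 0, 4 and 6; and 0, 4, 6 and 8.

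**The case against.** The strongest reply is that nothing here is invalid. Randomisation makes the unadjusted ANOVA a sound test, and the sample size was computed for that test and delivers what it claims. This stands: the point is about efficiency only.

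The repeated-measures ANOVA may use week 0, so it would be wrong to infer that no planned between-group analysis touches baseline. This also stands. But that analysis is not named as primary, and in its two-time form it is only a change-score comparison.

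The size of the gain is uncertain. The wide ISI entry range might suggest that baseline explains much of the endpoint variance, but the document gives no correlation, and the entry threshold of 10 truncates the range and may lower it. At r = 0.3 the gain is under 3 percentage points.

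On timing, the sentence in 3.7.1 follows demographics and vital signs, and eligibility already requires an ISI score. A reader might infer that baseline ISI is taken after allocation. The text does not say so; it only fails to exclude it.

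Finally, a short statistics section in an article may leave covariates to an analysis plan that is not shown. That would carry more weight if the article were silent, but it names the test, and the sizing matches that test without a covariate.

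**Conclusion.** The point holds as an avoidable loss of precision with two secondary clarifications. At 58 evaluable per arm, ANCOVA would lift omnibus power from 0.896 to between 0.92 and 0.98 for r from 0.3 to 0.6, or equivalently need 54 down to 38 per arm for 90% power. These figures rest on the protocol's means and SD and on an assumed r. The change-score figures (0.77, 0.83, 0.90 and 0.95 at r = 0.3, 0.4, 0.5 and 0.6) rest also on a baseline SD of 3.8. If change is what will be analysed, the stated 90% is missed below about r = 0.5 and met or exceeded above it.

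Two stronger readings are tempting and not supported. The omnibus test is not materially short of its stated power as planned. Nor would ANCOVA rescue the comparison of adjacent courses: for the 1-point difference between 4 and 6 weeks (two-sided 0.05, 58 per arm, no multiplicity correction), power is 0.29 unadjusted and only 0.32 to 0.43 for r from 0.3 to 0.6.

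**What to change.** - **3.10:** make the primary analysis an ANCOVA of end-of-treatment ISI on arm and baseline ISI. Treat PSQI, SAS, SDS and FSS the same way, each on its own baseline. Keep the one-way ANOVA as a sensitivity analysis.
- **3.5:** replace the reference to change with the post-treatment ISI score, which is what the 58 per arm is computed from. Under ANCOVA with baseline as covariate, analysing the score or the change gives the same treatment estimate, so the ambiguity stops mattering for the result.
- **3.7.1:** state that the baseline scales are completed within 48 h before randomisation and before allocation is disclosed.

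The cost is three short edits and one error degree of freedom. No new measurement is needed, and the sample size can stay as it is.

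### A three-arm repeated-measures ANOVA cannot use the unequal visit schedule: aligned on end of treatment it drops every mid-course reading, 3 of 15 assessments per A/B/C triple

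*Protocol article*

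**What the plan says.** Section 3.10 (Statistical analysis) gives one sentence to the longitudinal data: "Repeated measurements at different time points will be analyzed by using repeated-measures ANOVA". It does not say which time points form the within-subject factor, or whether the analysis is across arms or within each arm. The same section says that "the missing values will be supplemented by last observation carried forward (LOCF)", and names a separate test for group differences: "one-way analysis of variance (ANOVA) will be used for comparison inter-group comparison". The software is SPSS 26.0.

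The schedule, printed at the end of section 3.7.3.4, sets outcome assessments at "Group 1 (0, 4 weeks), Group 2 (0, 4, 6 weeks), Group 3 (0, 4, 6, 8 weeks), and at follow-up", with follow-up timed from each arm's own end of treatment (first and third month). The weeks match the treatment lengths in section 3.6, so Groups 1, 2 and 3 are read here as A, B and C. Table 2 puts the 4-, 6- and 8-week assessments in a single treatment-phase column. A sentence under the PSQI heading (3.7.3.1) places the primary endpoint at end of treatment and the secondary endpoint 3 months later.

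**The concern.** Classical repeated-measures ANOVA with group as a between-subject factor needs every participant to have the same set of occasions. This schedule gives the arms different numbers of visits at different weeks. Any three-arm version therefore has to leave out part of the scheduled data or create cells that were never scheduled.

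The readings at risk matter to the trial's question. The Introduction asks whether efficacy levels off after a certain course or keeps growing as the course lengthens. The week 4 and week 6 readings in Groups B and C, followed by their end-of-treatment readings, show that progression within the same participants. An analysis that cannot take them in loses the within-person part of the dose-effect evidence.

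**Working it through.** **The plan's own figure.** The sample size is checked first, to see whether it depends on this method. Inputs from section 3.5: means 10.5, 9.5 and 8.0, SD 3.8, k = 3. The grand mean is 28/3 = 9.333, and the squared deviations sum to 1.361 + 0.028 + 1.778 = 3.167. The table value ψ is not printed; 2.52 is assumed (n = 58 implies 2.522). Then n = 2.52² × 3.8² / (3.167/2) = 6.350 × 14.44 / 1.583 = 57.9, so 58 per group. The stated 67 follows as 58 × 1.15 = 66.7, and 3 × 67 = 201. The formula compares independent means, in line with one-way ANOVA. The repeated-measures method does not enter it.

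**Schedule on the randomisation clock** (assumption: 1 month = 30.4375/7 = 4.35 weeks):

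| Arm | Weeks from randomisation | Count |
|---|---|---|
| A | 0, 4, 8.3, 17.0 | 4 |
| B | 0, 4, 6, 10.3, 19.0 | 5 |
| C | 0, 4, 6, 8, 12.3, 21.0 | 6 |

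The total is 4 + 5 + 6 = 15 per A/B/C triple, or 67 × 15 = 1005 at full enrolment. Weeks 0 and 4 are the only ones common to all three arms. If a month is taken as 4 weeks, the follow-ups fall at weeks 8 and 16 (A), 10 and 18 (B), and 12 and 20 (C). Group A then shares week 8 with Group C, but still only weeks 0 and 4 are common to all three.

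**Ways to run repeated-measures ANOVA:**

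1. Shared weeks only (0 and 4). This uses 2 × 3 = 6 of 15 (67 × 6 = 402 of 1005). By week 4 each arm is scheduled for the same 12 sessions, so it carries no information on course length.
2. Four aligned occasions (baseline, end of treatment, +1 month, +3 months). This uses 4 × 3 = 12 of 15 (67 × 12 = 804). It drops 3 of 15 (20%; 201 of 1005): Group B week 4 and Group C weeks 4 and 6. Group A loses nothing, because its week 4 is its end of treatment. Of the 1 + 2 + 3 = 6 post-baseline treatment-phase readings per triple, half are dropped, and these are all of the mid-course ones. The aligned levels combine weeks 4/6/8, then about 8/10/12, then about 17/19/21.
3. Six labelled occasions (0, 4, 6, 8, +1 month, +3 months). This needs 67 × 18 = 1206 cells, of which 1206 − 1005 = 201 were never scheduled (134 in Group A, 67 in Group B). Without filling, a complete-case analysis would exclude all of Groups A and B.
4. Separate analysis within each arm. This uses all 15, but makes no comparison between courses.

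Of the three-arm versions (1 to 3), only the second compares completed courses without filled cells.

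**The case against.** The strongest reply is that the aligned analysis is the one the protocol points to. Table 2 has four columns common to every arm, and section 3.7.3.1 sets the endpoints at end of treatment and 3 months after it. Comparing completed courses is the trial's own question, and the unequal elapsed time comes from comparing courses of different length, not from the choice of ANOVA. All of this stands. A reader might infer that repeated-measures ANOVA is unworkable here, or that every way of running it is wrong. The documents do not support that.

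Second, section 3.10 never mentions a group-by-time interaction. It assigns group comparison to one-way ANOVA, so repeated-measures ANOVA could be meant within each arm, where nothing is lost. This also stands as a possible reading, but the longitudinal data would then say nothing directly about differences between courses.

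Third, a reader might infer that the carry-forward rule would fill Group A's weeks 6 and 8 with its week-4 score. The rule covers missing values, and a visit that was never scheduled is not a missing value. Nothing in the protocol says such cells would be filled.

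Fourth, this is a condensed article, and naming the time levels is commonly left to the full protocol or SAP. For the levels alone, that is fair. It does not remove the point: whatever levels a SAP names, the stated method cannot take all the scheduled assessments into a three-arm comparison, whereas another method in the same software can.

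**Conclusion.** The point holds as a limit on the longitudinal analysis. With 4, 5 and 6 assessments per arm, a three-arm repeated-measures ANOVA on completed courses uses 12 of 15 scheduled assessments and sets aside the 3 mid-course ones (20%; 201 of 1005 at 67 per arm). These counts assume full attendance. The 20% does not depend on how a month is converted to weeks.

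The point should not be read as undermining the main result. The end-of-treatment comparison appears to rest on one-way ANOVA, and the sample size reproduces without reference to repeated measures. The counts show data unused; they do not show bias or a changed conclusion. It is a change worth making because a better-fitting method is available at almost no cost.

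**What to change.** Replace the repeated-measures ANOVA sentence with a linear mixed model, which the named software can fit, using all observed scheduled assessments. Specify:

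- no carrying forward in this model, and an explicit statement that weeks not scheduled in an arm are not missing and are never filled;
- arm-specific visit means, with adjustment for the baseline score;
- a covariance that can be estimated with unequal schedules: a random participant intercept (compound symmetry), or an unstructured matrix estimated within each arm. A single unstructured matrix over calendar weeks is not estimable, because many pairs of weeks never occur in the same participant;
- arm contrasts at end of treatment and at 3 months after it;
- a description of the course over weeks 4 and 6 in Group B, and weeks 4, 6 and 8 in Group C;
- no three-arm contrast at a common calendar week after week 4, because no such week is scheduled.

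This is a change of analysis wording, with the same software, data and visits. It costs slightly more analysis work and relies on missing-at-random. It does not remove the difference in elapsed time: end-of-treatment contrasts still compare weeks 4, 6 and 8 by design, and the report should say so.
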